The intervention is aimed at mother-infant dyads and consists of 4 sessions delivered over the course of 4 weeks, at 2 hours per week. Each group will include a minimum of 3 and a maximum of 6 dyads per group led by a trained provider. The activities are protocolized in a manual and are designed to be carried out with the infant. The manual specifies the structure and content of each session, the details of the materials to be used, relevant aspects to be emphasized during the activities, and additional information that delves more deeply into the issues addressed in the workshop. This aims to ensure the comprehensive replication of the intervention, which has been associated with the best effectiveness in this type of intervention [34]. Table 1 shows the main components of the intervention.

The adaptation to the video conferencing format was carried out between May and July 2021 by 2 authors of the face-to-face intervention in conjunction with a designer experienced with digital interventions. We used the recommendations of the Early Intervention Foundation [21] to achieve good results in virtual interventions as a frame of reference, which include the use of engagement elements and mechanisms to improve adherence and flexibility.

We reviewed the complete content of the workshop, adjusted the sessions to 1.5 hours, and adapted the training manual and all the activities for use in a web-based group environment. We aim to provide lighthearted and interactive activities to allow all participants to understand and share their experiences. In addition, we have included some activities associated with the impact of the COVID- 19 pandemic. Figure 2 is a screenshot showing an example of a videoconference session, and Figure 3 shows 4 examples of activities that will take place in the workshop.

**Table 1 table1:** Main components of the intervention with the objectives and activities of each session outlined.

Session	Name	Objectives	Examples of activities
1	“Knowing each other around attachment”	Achieve group cohesion Provide knowledge about attachment Recognize expected affective behaviors in an infant	Dynamics of presentation Difficulties in motherhood Common myths on attachment and parenting

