**Figure 3 figure3:**
[figure not shown]
Screenshots illustrating different intervention activities. (A) Common myths in attachment and parenting; (B) working with different emotions and expressions in infants; (C) watching videos showing different parenting situations; (D) inventing a story from an image that shows the challenges of parenting.

In this study, each workshop will be led by a provider who is also a psychologist. Before conducting the intervention, the providers will receive a half-day training from the authors of the intervention. The video conferences will be recorded to guarantee the fidelity of the intervention and used later to perform a qualitative analysis of the change process [35].

To ensure internet connection during the evaluations and videoconferencing sessions, participants who do not have regular internet access will receive a prepaid card with internet gigabytes. To improve adherence to video conferencing sessions, the participating mothers will agree on the most convenient day and time for them to be held. In addition, a telephone chat group will be created to remind participants of the upcoming session and homework 1 day prior. If a participant cannot attend a videoconference session, they will be contacted by telephone by the provider to summarize the most important information of the session. This call will last between 15 and 20 minutes, and the main ideas and content of the session will be discussed, reinforcing the importance of positive interactions between mother and baby, sensitive care, and participation in the subsequent group sessions. For each participant to be considered to have received the intervention, they must attend at least 2 group videoconference sessions and 2 telephone calls or attend at least 3 of the 4 group video conference sessions.

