#### Feasibility of the Intervention

Feasibility will be evaluated in terms of the following factors: (1) eligibility rates, referring to the proportion of mothers who meet inclusion criteria compared with the total number of mothers contacted by telephone; (2) recruitment rates, meaning the proportion of mothers who accept the invitation to participate in the study with respect to those who meet eligibility criteria; (3) adherence to group intervention, meaning the proportion of participating mothers in the intervention arm that receive the intervention (at least 2 group video conference sessions plus 2 telephone calls) and the average number of online sessions attended; and (4) follow-up rates by treatment condition, which refers to the proportion of participants that completed the postintervention assessment

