### Sample Size

As this is a feasibility study, no hypotheses will be tested, and a formal power calculation is not required [44,45]. However, the evidence suggests a sample size of 25 people per arm for a small effect size of 0.2, which is suitable for clinical feasibility trials [45]. Therefore, a sample size of 50 participants was established, and the 3:2 allocation was chosen considering possible partial adherence to the intervention.

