## Discussion

### Expected Findings

The objective of this study is to assess the feasibility and acceptability of the C@nnected group videoconferencing intervention, which aims to improve maternal sensitivity in mother-infant dyads attending PHC centers in Chile and was adapted from a face-to-face intervention. We expect to find an adequate feasibility of this intervention in terms of achieving good recruitment rates (around 60% mothers will accept the invitation to participate in the study with respect to those who meet eligibility criteria), good adherence to group intervention (around 60% in the intervention arm will receive the intervention), and adequate adherence to the sessions (the average expected attendance is 3 out of 4 sessions). We expect to find a very good acceptability of the intervention with high scores in the satisfaction questionnaire and positive evaluation in the qualitative assessment. We also expect to find favorable results of the intervention in terms of clinical outcomes, especially relating to maternal sensitivity, which will allow us to estimate the sample size for the future RCT to evaluate effectiveness. The results of this study will inform the key parameters for the implementation and evaluation of the intervention and facilitate the design of an effectiveness study in the future.

The COVID- 19 pandemic has led health teams to adapt some interventions to the eHealth format, and it is likely that many of these interventions will remain in this format even after the pandemic is over. Nevertheless, we should not assume that interventions will work equally as well when delivered through virtual methods. Existing interventions must be carefully adapted and include a focus on identifying the core components that must be maintained [21].

Internationally, there are some group parenting interventions with proven efficacy to increase maternal sensitivity; however, one of the main problems of this type of intervention is low adherence [48]. The development of eHealth interventions may improve the accessibility and flexibility of group-based interventions, which are important for parents. If this group intervention delivered by videoconference is shown to be feasible, it will be particularly useful for mothers that face barriers to attending face-to-face interventions.

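### The primary adherence proportion omits the route of attending at least 3 of the 4 sessions, so read literally it counts mothers with 3 or 4 sessions as not having received the intervention

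*Protocol article*

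**What the plan says.** The article defines receipt of the intervention twice.

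- **Interventions, Intervention Arm (text after Figure 3).** To count as having received the intervention, a mother must "attend at least 2 group videoconference sessions and 2 telephone calls or attend at least 3 of the 4 group video conference sessions". This gives two alternative routes.
- **Primary Outcome Measures, Feasibility of the Intervention, item 3.** Adherence is the proportion of intervention-arm mothers who "receive the intervention (at least 2 group video conference sessions plus 2 telephone calls) and the average number of online sessions attended". Only the first route appears.

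Three other statements bear on the comparison.

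- The programme "consists of 4 sessions delivered over the course of 4 weeks" (Intervention Arm).
- On calls: "If a participant cannot attend a videoconference session, they will be contacted by telephone by the provider" (Intervention Arm). No section provides these calls to a mother who attended. Session reminders go through a chat group and are a separate matter.
- Expected Findings anticipates "good adherence to group intervention (around 60% in the intervention arm will receive the intervention", and says that "the average expected attendance is 3 out of 4 sessions".

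**The concern.** Dropping the second route is not a harmless abbreviation, because calls and attendance trade off against each other. A mother becomes eligible for a call only by missing a session. A rule that requires 2 calls therefore requires 2 missed sessions, and it excludes the mothers with the best attendance.

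The affected quantity is one of the listed primary feasibility measures. The article sets an expected value for it and intends the results to inform a later effectiveness trial. With two different definitions in the text, the reported proportion depends on which one the analyst picks up, and that choice would remain open after the attendance data are known.

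**Working it through.** **Inputs.** 4 sessions and calls for missed sessions only (Intervention Arm); the two receipt rules quoted above; about 60% receipt and mean attendance of 3 (Expected Findings); and "a sample size of 50 participants was established, and the 3:2 allocation was chosen" (Sample Size), which gives 50 × 3/5 = 30 intervention mothers. The article does not derive its 60%, so there is no calculation to reproduce. The check is whether each rule is coherent and compatible with the stated expectations.

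**Step 1: classify every attendance level.** With one call per missed session, calls ≤ 4 − sessions attended.

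| Sessions attended | Most calls possible | Can meet outcome wording | Can meet two-route rule |
|---|---|---|---|
| 0 | 4 | no | no |
| 1 | 3 | no | no |
| 2 | 2 | yes, with both calls | yes, with both calls |
| 3 | 1 | no | yes |
| 4 | 0 | no | yes |

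Under the outcome wording, only the row with exactly 2 sessions can qualify. If all 30 mothers attend all 4 sessions, the result is 0/30 = 0%, against 30/30 = 100% under the two-route rule.

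**Step 2: test against the stated expectations.**

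- *Outcome wording.* If 60% qualify, each has exactly 2 sessions. The other 40% have at most 4, so the mean is at most 0.6 × 2 + 0.4 × 4 = 2.8, below 3. Reaching 3 would need the other 40% to average (3 − 0.6 × 2)/0.4 = 4.5 sessions out of 4. Equivalently, if a share s attends exactly 2 and the mean is 3, the largest possible s solves 2s + 4(1 − s) = 3, so s = 50%.
- *Two-route rule.* Receivers can have up to 4 sessions. Non-receivers have at most 2 (2 sessions without both calls). The mean is at most 0.6 × 4 + 0.4 × 2 = 3.2. A mean of 3 is attainable if receivers average at least (3 − 0.4 × 2)/0.6 = 3.67 sessions.

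**Step 3: illustrate the gap at less extreme attendance.** Assume, for illustration only, that sessions attended follow Binomial(4, p). The article gives no attendance distribution; p = 0.75 matches its mean of 3. The outcome wording yields at most P(2). The two-route rule yields P(3) + P(4) if no call is completed, and P(2) + P(3) + P(4) if every call is.

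| Assumed p | Mean sessions | Outcome wording, at most | Two-route rule |
|---|---|---|---|
| 0.60 | 2.4 | 34.6% (about 10 of 30) | 47.5% to 82.1% |
| 0.75 | 3.0 | 21.1% (about 6 of 30) | 73.8% to 94.9% (about 22 to 28 of 30) |
| 0.85 | 3.4 | 9.8% (about 3 of 30) | 89.0% to 98.8% |

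Across these three rows, the ceiling under the outcome wording falls as attendance rises, while the two-route proportion rises.

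**The case against.** The strongest reply is that the parenthesis in the outcome definition is shorthand. The Intervention Arm section states the operative rule in full. The outcome reuses the same concept and cites only the minimum qualifying exposure. The expectations in Expected Findings fit the two-route rule and not the shorter one, which suggests that the authors had the full rule in mind. Both rules also use the same per-mother counts of sessions and calls, so either proportion can be recovered, and randomisation and sample size are untouched.

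Most of this stands as evidence of intent. It does not remove the contradiction: the outcome section is where an analyst would look for the definition, and what it says there gives a different number. A fuller protocol or analysis plan may carry the complete rule, but the article itself states two that differ.

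Three stronger inferences are tempting, and the article does not support them.

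- *The measure falls whenever attendance improves.* It rises when a mother moves from 0 or 1 session to 2 sessions with 2 calls. It falls only above 2 sessions.
- *A well-attended programme could be declared infeasible.* The article sets no stop/go threshold. The 60% is an expectation, adherence is one of four feasibility factors, and mean sessions is reported in the same item. A 0% beside a mean of 4.0 would be noticed.
- *Low adherence to the face-to-face version is a main reason for the trial.* The rationale given is restricted face-to-face access during the pandemic. Low adherence appears as an earlier result (Chilean Context) and as a known problem of such group interventions (Expected Findings).

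**Conclusion.** The two definitions conflict, and the one attached to the primary outcome is wrong as written. Followed literally, it scores mothers with 3 or 4 sessions as not having received the intervention. The extreme case is 0% against 100% of 30. At the article's own mean of 3 sessions, no more than 50% could qualify under any attendance pattern, and at most about 21% under the illustrative binomial pattern.

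The conclusion assumes that the 2 calls are the provider's summary calls for missed sessions, at most one per session, as the article describes them. If two calls could be made for one missed session, a mother with 3 sessions could qualify and the 2.8 limit would no longer hold. A mother with full attendance would still fail.

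The practical consequence is a misreported primary proportion and an avoidable choice of definition after the data are in. It is not a flawed feasibility decision, since no decision rule rests on this figure.

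**What to change.** In Feasibility of the Intervention, item 3, replace the parenthesis with the full receipt rule from the Intervention Arm section (at least 3 of the 4 group sessions, or at least 2 group sessions with 2 telephone calls), or with an explicit cross-reference to it. One definition should then govern both the primary proportion and the 60% in Expected Findings; Step 2 shows that the 60% and the mean of 3 can both hold under that rule.

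Reporting the two routes separately is optional. It would show how much of the receipt depends on telephone replacement.

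The cost is one sentence of wording. No new data are needed, because both rules already require each mother's session and call counts.

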#### Acceptability of the Intervention (Quantitative Assessment)

Satisfaction with the intervention will be measured with the Spanish version of the Credibility/Expectancy Questionnaire (CEQ) [36] at the preintervention assessment (t0) and 2 to 3 months later in the postintervention assessment (t1) for both arms of the study. This is a self-report instrument that comprises 6 items scored on a 9-point Likert-type scale ranging from 1 (not at all) to 9 (very) as well as 2 factors (credibility and expectation) that explain 82.46% of the variance. In terms of reliability, the total questionnaire showed a Cronbach α of .8, and scores range from 0 to 100, with higher scores indicating higher acceptability of the intervention.

#### Acceptability of the Intervention (Qualitative Assessment)

This measure will evaluate the experience of all participants of the intervention, both those providing the intervention and the mothers participating in the workshops, to determine which factors are associated with acceptability, barriers, and facilitators to implementation. This will be carried out as follows:

First, semistructured interviews will be conducted with the providers of the intervention. These interviews will inquire about the changes, achievements, and learning observed in the participants, the most and least valued topics and methodologies, difficulties in implementation and how it could be integrated into standard practice, possible improvements to the intervention, and core components of the intervention.

Second, focus group interviews with mothers participating in the intervention will be carried out. Two focus groups, each including 4 to 6 mothers, will be asked about their opinions regarding the usefulness of the intervention, changes, achievements, learning experiences, satisfaction, most and least valued topics and methodologies, and possible improvements. The aim of this focus group interview is to collect information on participants’ experience and identify possible improvements and the core components of the intervention.

#### Secondary Outcome Measures

Clinical outcomes measures will be carried out to characterize the sample and estimate how the intervention could guide the sample size of the next effectiveness study. These clinical outcome measures will be assessed at the preintervention assessment (t0) and 2 to 3 months later in the postintervention assessment (t1). Table 2 shows the schedule of enrollment, interventions, and assessments, and Figure 4 shows the study design schema.

**Table 2 table2:** Schedule of enrollment, interventions, and assessments.

Scheduled items		Study period				
		Enrollment	Preintervention assessment	Allocation	Intervention	Postintervention assessment
Time point		t0	t0			t1
**Enrollment**						
	Eligibility screen	✓				
	Informed consent	✓				
	Initial evaluation		✓			
	Allocation			✓		
**Interventions**						
	Intervention group (TAU^a^ + group videoconference intervention)				✓	
	Control group (TAU + educational brochures)				✓	
**Assessments**						
	Feasibility	✓	✓		✓	✓
	Acceptability: quantitative evaluation (CEQ^b^)		✓			✓
	Acceptability: qualitative evaluation					✓
	Clinical outcomes (ESA^c^, EPDS^d^, ASQ:SE-2^e^, MPAS^f^)		✓			✓

^a^TAU: treatment as usual.

^b^CEQ: Credibility/ Expectancy Questionnaire.

^c^ESA: Escala de Sensibilidad del Adulto (Adult Sensibility Scale).

^d^EPDS: Edinburgh Postnatal Depression Scale.

^e^ASQ:SE-2: Ages and Stages Questionnaire: Social-Emotional.

^f^MPAS: Maternal Postnatal Attachment Scale.

**Figure 4 figure4:**
[figure not shown]
Study design schema. ASQ-SE-2: ages and stages questionnaire, social -emoaitonal; CEQ: measurement of credibility/expectancy questionnaire; ESA: adult sensibility scale; EPDS: Edinburgh postnatal depression scale; MPAS: maternal postnatal attachment scale; TAU: treatment as usual.

The secondary outcome measures are listed as follows.

#### Changes in Maternal Sensitivity

Changes in maternal sensitivity will be measured with the Escala de Sensibilidad del Adulto (ESA), also known as the Adult Sensitivity Scale [37]. Maternal sensitivity is the primary outcome that will also be measured in the effectiveness study since the objective of the intervention is to improve maternal sensitivity. This scale assesses an adult’s sensitivity in their interaction with children between 6 and 36 months of age. The mother and child are filmed for 5 minutes during free play interaction. The only instruction given is “do what you always do.” The coding system considers a rubric with 19 indicators that are related to different aspects of the sensitivity response. Each indicator is given a score between 1 and 3, with a higher score indicating higher sensitivity. In terms of reliability, the Cronbach α of the instrument is .93. The coders will be external to the research and blind to the randomized group, sociodemographic variables, and results of the different measurements. The Cohen kappa coefficient between the encoders will be obtained for the first 20 videos.

##### Changes in Maternal Depressive Symptoms

The measurement of postpartum depressive symptoms is of great relevance given its important association with low maternal sensitivity. This will be measured with the Edinburgh Postnatal Depression Scale (EPDS) [38], which is globally used to screen for maternal depression [39]. It consists of a self-administered questionnaire containing 10 multiple-choice questions, with 30 points as the maximum score and higher scores indicating higher depressive symptomatology. The scale has been validated in Chile [40] and has a sensitivity of 100%, a specificity of 80%, and adequate internal consistency (Cronbach α=.77). We will use the cutoff point of ≥10 to consider the presence of postpartum depressive symptoms.

#### Changes in Infants’ Socioemotional Development

The measurement of socioemotional development will allow for a more direct evaluation of the effects of the intervention on the participating infants. These will be measured with the Spanish version of the Ages and Stages Questionnaires: Social-Emotional (ASQ:SE-2) [41]. Several studies have consistently supported the precision and ease of use of ASQ-SE-2, which has been used widely in early mental health intervention programs [42]. We will use the 6- and 12-month versions. A higher score indicates worse socioemotional development. Each version has its specific cutoff score, and those with scores higher than the cutoff are considered to be “at risk for socioemotional development delay.”

#### Changes in Postpartum Maternal Bonding

The measurement of maternal bonding will allow us to chracterize the sample and evaluate possible changes to this parameter due to the intervention. We will use the Spanish version of the Maternal Postnatal Attachment Scale (MPAS) [43], a self-report measure that has 19 items ranging from 1 (low bonding) to 5 (high bonding) and is divided into 3 factors: quality of bonding, absence of hostility, and pleasure in interaction. Psychometric properties of the original version of the scale have shown an adequate internal consistency (Cronbach α=.78).

### Participant Timeline

The study duration for the participants will be 3 months, regardless of study arm allocation. This study does not have a follow-up phase. The total trial data collection period will be approximately 14 months.

### Sample Size

As this is a feasibility study, no hypotheses will be tested, and a formal power calculation is not required [44,45]. However, the evidence suggests a sample size of 25 people per arm for a small effect size of 0.2, which is suitable for clinical feasibility trials [45]. Therefore, a sample size of 50 participants was established, and the 3:2 allocation was chosen considering possible partial adherence to the intervention.

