## Methods

### Trial Design

This is a data analyst–blind, superiority, pilot feasibility study with a mixed design. The quantitative component is a 2-arm randomized parallel group of 50 mothers of infants aged 6-12 months who receive health care in 2 PHC centers in Santiago, Chile. Mothers will be randomized into the intervention or control group in a to 3:2 ratio (with more people allocated to the intervention arm). Both groups will receive the usual treatment and educational brochures provided by the PHC center, with the intervention group also receiving the C@nnected videoconferencing intervention. The qualitative component will consist of semistructured interviews with intervention providers to identify possible improvements and core components of the intervention as well as focus groups with mothers participating in the intervention to evaluate user acceptability and satisfaction with the implementation.

This type of study is suggested by the literature as an initial requirement for the implementation of an innovative intervention before applying it on a larger scale. It is also recommended to use quantitative and qualitative methodologies to evaluate feasibility and acceptability [29]. This clinical trial protocol follows the SPIRIT (Standard Protocol Items: Recommendations for Interventional Trials) and [30] and CONSORT (Consolidated Standards of Reporting Trials) guidelines [31]. Figure 1 provides a flowchart of the study process.

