### Assignment of Interventions

#### Sequence Generation

To generate the random allocation sequence, we will use a computer software program called Studyrandomizer using permuted block randomization with a block size of 5 in a 3:2 ratio.

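### The total of 50 is built on a guide of 25 per arm, but 3:2 allocation gives 30 and 20, so the control arm starts 5 mothers below that guide (minor)

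*Protocol article*

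**What the plan says.** The Sample Size section of the protocol article first says that no hypotheses will be tested and that a formal power calculation is not needed. It then cites a guide: "the evidence suggests a sample size of 25 people per arm for a small effect size of 0.2". The next sentence draws the total from it, "Therefore, a sample size of 50 participants was established", and continues with the ratio: "the 3:2 allocation was chosen considering possible partial adherence to the intervention".

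The ratio is the same elsewhere. The Abstract and the Trial Design section both give 3:2 in favour of the intervention arm, and the Sequence Generation section specifies "permuted block randomization with a block size of 5 in a 3:2 ratio". The Results section says that enrolment continues until 50 participants are reached. The article text never states the arm sizes that follow, and it does not say that one of them lies below 25.

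**The concern.** The per-arm figure and the allocation ratio do not fit together. A guide of 25 in each arm leads to 50 only under equal allocation. Once 3:2 is applied to the same total, one arm lies above the guide and the other below it. The section moves from the guide to the total with a conclusion word and then changes the ratio without going back to the guide.

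The stated size is therefore one that the design does not deliver in the control arm. That arm matters here for two reasons. Follow-up is to be reported by treatment condition as one of the primary feasibility measures. The clinical outcomes are also meant to inform the sample size of the later effectiveness trial, for which the spread of scores in an arm without the intervention is a natural input. A reader who takes the 25 at face value would expect both to rest on 25 control mothers.

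**Working it through.** **Inputs, all from the protocol article**

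- Guide: 25 per arm (Sample Size).
- Total: 50 (Sample Size, Trial Design, Results).
- Allocation: 3:2, larger share to the intervention (Abstract, Trial Design, Sample Size).
- Block size: 5 (Sequence Generation).
- Expected adherence in the intervention arm: about 60% (Expected Findings).

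**1. The plan's own total**

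2 × 25 = 50. The stated total is reproduced exactly, but only with equal arms.

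**2. Arm sizes under the stated allocation**

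- Intervention: 50 × 3/5 = 30.
- Control: 50 × 2/5 = 20.
- 50 / 5 = 10 complete blocks, each with 3 intervention and 2 control places, so a single sequence gives exactly 30 and 20.
- Against the guide, the intervention arm is 30 − 25 = 5 above. The control arm is 25 − 20 = 5 below, and 5/25 = 20%.

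**3. Effect on the comparison between arms**

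For a common standard deviation, the equal-arm size with the same precision is 2·n₁·n₂/(n₁ + n₂) = 2 × 30 × 20/50 = 24 per arm.

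The standard error of a standardised difference is √(1/n₁ + 1/n₂):

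| Arms | Standard error | 95% half-width (1.96 × SE) |
|---|---|---|
| 25 and 25 | 0.283 | 0.554 |
| 30 and 20 | 0.289 | 0.566 |

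The ratio is 0.2887/0.2828 = 1.02, so the standard error is about 2% larger.

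**4. Effect on estimates from one arm alone**

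The standard error of a mean or proportion scales with 1/√n. For the control arm, √(25/20) = 1.12, about 12% larger than with 25 mothers. For the intervention arm, √(25/30) = 0.91, about 9% smaller. The loss is therefore concentrated in the control arm.

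**5. Illustration for an arm-specific feasibility rate**

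The Expected Findings section anticipates that "around 60% in the intervention arm will receive the intervention". On 30 mothers this is 0.6 × 30 = 18. The 95% Wilson interval for 18/30 is 42% to 75%.

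**6. For scale only, not as a proposal**

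Twenty-five controls at 3:2 would need 25 × 5/2 = 62.5, that is 63 mothers (38 and 25), or 65 in whole blocks of 5 (39 and 26).

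**The case against.** The strongest reply is that 25 is not a requirement. The section disclaims a power calculation and offers the figure as something the evidence suggests, so it is a guide used to reach a round total. The multiplication itself is correct. The unequal ratio is disclosed in the very sentence that fixes the total, with a reason, and anyone can see that the arms will differ. The precision lost in the comparison is about 2% in standard error. All of this stands, and it is why the point is minor. What does not stand is the reason as a full explanation: concern about partial adherence supports more than 25 in the intervention arm, but on an unchanged total it says nothing about why 20 controls are enough.

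Three stronger readings are tempting and are not supported.

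- *The trial is underpowered for an effect of 0.2.* Under an assumed two-sided 5% test, 25 per arm would have about 10.5% power at 0.2 and 30/20 about 10.3%. The article claims no power and plans no hypothesis test in its sample size section, so neither figure contradicts it.
- *The size ignores loss to follow-up.* No allowance is stated, but whether the cited guide already contains one depends on a source that is not at hand. The Results section can also be read as continuing until 50 participants have data. Any loss rate would be an assumption brought from outside. Even if lost mothers were replaced, the split would stay near 30 and 20.
- *The justification is of the wrong kind and must be replaced by one based on the precision of the feasibility rates.* Estimating a clinical effect size is a stated secondary aim, so citing one is not out of place. Intervals for feasibility proportions may be left to the full protocol or the analysis plan, and their absence from an article is not a fault. Eligibility and recruitment rates do not depend on the 30/20 split at all.

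**Conclusion.** The inconsistency is certain and small. The total of 50 follows from 25 per arm only at 1:1. The 3:2 ratio adopted in the same sentence gives 30 and 20, leaving the control arm 5 mothers (20%) under the cited figure at randomisation, without acknowledgement and without a reason that covers it. The comparison between arms is hardly touched: the equivalent is 24 per arm, with a standard error about 2% larger. Estimates from the control arm alone have a standard error about 12% larger than 25 mothers would give.

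This rests on the stated total, ratio and block size, on one allocation sequence filled to 50, and, for the precision figures, on a common standard deviation in the two arms. No loss rate is assumed. Severity: minor, a correction of wording in the sample size rationale.

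**What to change.** Restate the Sample Size section so that the rationale matches the design. Suggested wording:

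> Fifty mothers will be randomised 3:2, giving 30 in the intervention arm and 20 in the control arm. The guide of 25 per arm is exceeded in the intervention arm and not met in the control arm. For the comparison between arms, this is equivalent to 24 per arm under equal allocation. The larger intervention arm was chosen because adherence may be partial.

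If the published article cannot be changed, put the same statement in the analysis plan and the results report.

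Optionally, report the arm-specific feasibility rates with 95% intervals, with denominators of 30 and 20 shown, for example 42% to 75% for adherence of 18/30. This is a reporting choice and not needed to cure the inconsistency.

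The cost is a few sentences. No extra participants are needed, and the total, the randomisation and the planned analysis stay as they are. The stated position becomes slightly less favourable, because it concedes that one arm is below the guide.
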